## Results

### Ethics and Collection of Data

Ethical approval for this study has been received from the Health and Disability Ethics Committee of New Zealand. The recruitment and collection of data will begin in September 2021. We aim to complete data collection by June 2022. Statistical analyses, report writing, and dissemination of results are expected to be completed by February 2023. Funding is being sought for the study.

### Expected Benefits or Outcomes

The anticipated outcomes of this study are a reduction in bone turnover as measured using CTx-I as a marker, as well as a reduction in inflammation (reduced or changed levels of specific cytokines such as hs-CRP, IL-6, and TNF-α).

With menopause and the loss of estrogen, bone turnover (formation and resorption) increases significantly. Over time, because of increased levels of IL-6 and inflammation, bone resorption (breakdown) overtakes bone formation, and this increase in bone resorption can be measured using the marker CTx-I. Several studies over the past 20 years have shown that a reduction in CTx-I is associated with long-term changes in bone density and a reduction in fractures. CTx-I most sensitively reflects the change in bone resorption after mineral supplementation or increased absorption of calcium and can predict the rate of bone loss and fracture risk in postmenopausal women. CTx-I may reflect parameters of bone strength unrelated to BMD, such as microarchitectural deterioration of bone tissue resulting in microcracks that act as stress risers or trabecular perforation.

Supplementation with a synbiotic will modify the gut microbiota and improve calcium and magnesium absorption. Prebiotic supplementation promotes bacterial growth that induces nondigestible carbohydrate fermentation, increases short-chain fatty acids (SCFAs), and reduces the pH of the gut, thereby increasing calcium absorption. The reduction in pH promotes the growth of bacteria that are less likely to cause inflammation, and SCFAs stimulate the effects of anti-inflammatory cytokines. Probiotic supplementation by *Lactobacillus* and *Bacillus* species may promote an immunoprotective response in the gut mucosa by reducing the levels of systemic inflammatory cytokines and preventing the reduction in bone density.

## Discussion

### Principal Findings

Degeneration of bone health in the form of osteoporosis, osteoporotic fractures, and osteoarthritis are major health care issues leading to a significant increase in morbidity and mortality in New Zealand and all over the world. Similarly, the growing number of patients with osteoporosis or osteoarthritis results in huge health care costs. The aim is to measure the effect of synbiotics, weight-bearing exercises (10,000 brisk walking steps per day), or a combination of both on gut microbiota, inflammation status, and bone health. This study is important for several reasons. This study is directed toward postmenopausal women who have experienced a rapid phase of bone loss 5 years postmenopause. The use of a synbiotic (a combination of probiotic and prebiotic) supplement is particularly novel in the modulation of the immune system, gut microbiota, and anti-inflammatory response. Studies are needed to measure the effects of synbiotic supplementation and weight-bearing exercise on gut microbiota, inflammatory status, and bone health. Randomization by exercise history will help eliminate the effects of the previous exercise regime for the study. There is a critical need for measures of bone turnover and not BMD only as a primary outcome.

The effects of probiotic or synbiotic supplementation on markers of inflammation have also been reported. A reduction in proinflammatory cytokines (eg, IL-1β, TNF-α, IL-6, and IL-8) and an increase in anti-inflammatory cytokines (IL-10 and IL-4) [44] were observed in response to these interventions. Similarly, studies have indicated the protective factors of probiotic supplementation [45] and exercise in bone metabolism and health [34]. Long-term participation in a relevant and targeted exercise regime is known to improve bone mechanical properties over time [46].

### Synbiotics: Mechanism of Action

Prebiotic supplementation promotes bacterial growth that induces nondigestible carbohydrate fermentation, increases SCFAs, and reduces the pH of the gut contents, thereby increasing calcium absorption. The reduction in pH promotes the growth of bacteria that are less likely to cause inflammation, and SCFAs stimulate the effects of anti-inflammatory cytokines. In addition, probiotic supplementation with *Lactobacillus* and *Bacillus* species promotes immunoprotective response or effects in the gut, reducing inflammatory cytokines and preventing the reduction in bone density [47].

### Markers of Bone Turnover

Prediction of bone loss and risk of fractures is conducted using biomarkers of bone turnover independent of bone density in women. The occurrence of menopause results in a period of bone loss, where the rate of bone resorption exceeds that of formation (approximately 5 years). A bone remodeling cycle of formation and resorption takes place between 4 and 6 months, replenishing approximately 5%-15% of the total bone mass in a year [46]. These data provide the rationale for the length of time and a comprehensive investigation of body composition and bone turnover status in the study described here.

The strength of the RCT will account for exercise history and the sample size and duration to ensure an adequately powered sample needed to detect clinically and statistically significant results.

### Ethics and Dissemination

#### Ethics

The study received ethical approval from the Health and Disability Ethics Committee of New Zealand.

#### Safety and Data Monitoring

The principal investigator and team will monitor the conduct, safety, and scientific integrity of the proposed clinical trial. Routine laboratory measurements, including liver and kidney function tests, blood glucose (nonfasting), and lipid profile (triglyceride, total cholesterol, high-density lipoprotein cholesterol, and low-density lipoprotein cholesterol) tests, will be performed at baseline and 12 weeks. Individuals with results that are outside the clinical range will be contacted and referred to their general practitioner. The safety precaution will be to inform all participants to report any effects of treatment, and in the unlikely event that 20% of the participants report severe diarrhea, a discontinuation of the study will be triggered. Each report will include the monitoring of compliance with informed consent and eligibility requirements, compliance with the recruitment plan according to protocol, follow-up data collection according to the protocol, expected and actual accrual, protocol violations, and patient withdrawals from the study.

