### Physical Activity

Physical activity is defined by the World Health Organization as any “bodily movement of the skeletal muscle, which requires energy expenditure” [26]. Physical activity enhances the composition and function of the human skeletal system. However, skeletal muscle performance also deteriorates with age [27], and a lack of exercise and physical activity has been linked to bone loss and ultimately osteoporosis [28]. Osteoporosis may cause falls that result in osteoporotic fractures in older women.

Previous studies, including Cochrane reviews, have reported the effects of physical activity on bone strength across the life spans [29] of children and adolescents [30] as well as women, especially postmenopausal women [31-33]. A study from Italy reported progressive resistance strength training of the lower limbs to be most effective for the neck of the femur BMD in patients with osteoporosis. In contrast, a multicomponent training program was suggested for a spine BMD intervention [34].

Neilson et al [35] have defined activity energy expenditure (AEE) as “a modifiable component of total energy expenditure (TEE) derived from both volitional and non-volitional activities.“ Total energy expenditure comprises multiple components, including physical activity energy expenditure, resting energy expenditure, and the thermic effect of food [36]. The impact of physical activity has been used to alleviate several obesity-related diseases and the overall burden of diseases in men and women alike [37].

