Therefore, modulation with a synbiotic food supplement and weight-bearing low-impact exercise (interventions) can be used to provide data that may contribute to improvements in osteoporotic patient care. This study will use a prospective stratified (by exercise history), randomized, 4-group experimental design with 2 major data collection points (baseline and week 12). Before randomization, participants will be stratified by exercise history (≥2 high-intensity exercise sessions per week and <2 sessions per week) using the International Physical Activity Questionnaire to ensure equal distribution among the 4 groups. However, all participants would be permitted to continue their usual physical activity regime.

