## Methods

### Participants

The G*Power statistical software, version 3.1.9.7, developed in Heinrich Heine University Düsseldorf, was used to calculate the sample size using the bone biomarker CTx-I; a recommended number of 36 women would be required for the study. However, 40 women aged >60 years will be recruited for each of the 4 groups to allow for a possible dropout rate of 10%. The test groups will receive the synbiotic food supplementation and exercise program (10,000 steps brisk walking per day required), whereas the control group will receive a placebo and no exercise; however, dietary intake and exercise will be monitored by a 3-day diet diary and the International Physical Activity Questionnaire. All study participants will read the information sheet, and signed and written consent forms will be obtained from them.

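### The severe-diarrhea stopping rule depends on unsolicited, self-attributed symptom reports, and its count is not among the listed monitoring-report contents

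*Protocol article*

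**What the plan says.** All the relevant safety text stands in one paragraph of the protocol article, under Safety and Data Monitoring.

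- **Symptoms:** "The safety precaution will be to inform all participants to report any effects of treatment". No scheduled symptom question is described.
- **Laboratory safety:** "Routine laboratory measurements, including liver and kidney function tests, blood glucose (nonfasting), and lipid profile", which "will be performed at baseline and 12 weeks". Women with out-of-range results are contacted and referred.
- **Stopping rule:** "in the unlikely event that 20% of the participants report severe diarrhea, a discontinuation of the study will be triggered". No denominator or review time is given.
- **Monitoring report:** "Each report will include the monitoring of compliance with informed consent and eligibility requirements". The list continues with recruitment, follow-up data collection, accrual, protocol violations and withdrawals. Adverse events and the diarrhea count are not on it.
- **Oversight:** the principal investigator and team are to monitor safety.

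Elsewhere, the Overview describes a "4-group experimental design with 2 major data collection points (baseline and week 12"), and Table 1 has columns for those two times only. The Participants section describes an "exercise program (10,000 steps brisk walking per day required"). It gives the control group a placebo and no exercise.

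**The concern.** A rule that can end the study needs a reliable count of the event it acts on. Here the count is built from what women choose to report, and they are asked for effects of treatment rather than for symptoms. A woman who puts her diarrhea down to something she ate has, on the wording, nothing to report. The count that does arise is then missing from the listed contents of the report through which the trial is monitored.

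The same filter bears on comparisons between arms. Women know whether they were told to walk, so a stumble or a sore knee may be seen as treatment-related in one arm and as ordinary in another. The exercise arms hold 80 of the 160 women. The article's Conclusions look ahead to offering the combined intervention as a noninvasive approach, and evidence on tolerability would belong beside any such statement.

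**Working it through.** **1. Reproduce the plan's numbers.** The Statistical Analyses section gives 36 per group and 10% dropout: 36 / (1 − 0.10) = 40 per group, and 4 × 40 = 160. Both agree with the article.

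**2. Size of the trigger.** Taking all 160 women as the denominator (an assumption, since the article names none), 0.20 × 160 = 32 reports. If every report came from the two synbiotic arms (2 × 40 = 80 women), that would be 32 / 80 = 40% of them.

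**3. Effect of incomplete reporting on the threshold.** If a fraction r of affected women report, a 20% reported share corresponds to a true share of 20% / r. The values of r are assumptions; the article gives no reporting rate.
- r = 0.75: 0.20 / 0.75 = 27%
- r = 0.50: 0.20 / 0.50 = 40%
- r = 0.25: 0.20 / 0.25 = 80%

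**4. Chance of ever reaching 32 reports.** Reports are the sum of two independent binomials, Bin(80, r × p) for the synbiotic arms and Bin(80, r × 0.02) for the other two. The synbiotic rate p, the 2% background rate and r are all assumed. The probability of 32 or more was computed exactly.

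| True rate p | True pooled share | r = 1 | r = 0.75 | r = 0.50 |
|---|---|---|---|---|
| 40% | (32 + 1.6) / 160 = 21% | 67% | 7% | about 0.01% |
| 50% | (40 + 1.6) / 160 = 26% | 99% | 47% | 0.5% |

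In both rows the expected true share exceeds 20%. The 67% with full reporting reflects chance variation around a share only just above the threshold; the fall along each row is due to reporting alone.

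**5. Rule against report.** The rule needs the number of women who have reported severe diarrhea, set against the number of participants. The listed report contents include accrual, which bears on the second number, but nothing that supplies the first. This mismatch needs no assumption about r.

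**The case against.** The strongest reply is that this is a condensed article. Adverse-event forms and contact schedules commonly sit in the full protocol, Table 1 is headed as a table of outcome measures, and the report list is not said to be exhaustive. This stands to a degree: a missing form or table row would not by itself be a finding. It does not remove the point, because the article chose to state the collection method, the rule and the report contents together, and as stated they do not fit.

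It is also fair that the rule is worded in terms of reports, so on a literal reading an unreported case does not count towards it. But a rule about severe diarrhea is useful only so far as reports follow occurrence, and the literal count is still absent from the list.

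Several stronger readings are tempting and should not be drawn:

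- **That harms are captured only if a woman volunteers them.** Laboratory safety tests are scheduled for everyone at both time points.
- **That the rule cannot be applied in time.** Spontaneous reports can arrive on any day, the team monitors safety, and calling the two time points major does not exclude other contact.
- **That harms cannot be compared between arms.** Laboratory results can be compared, and reports can be tabulated by arm, though with a risk of bias. Aims 1 to 4 include no formal comparison of harms.
- **That the article names falls as the key risk of the trial.** The Physical Activity section says "Osteoporosis may cause falls that result in osteoporotic fractures in older women", as background on osteoporosis. The exclusion criteria remove women with a T score below −2.5 or a fragility fracture in the previous 6 months.
- **That exercise-only women know they take no supplement.** The article does not say whether that arm receives placebo. Only awareness of the exercise assignment is evident.

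**Conclusion.** The point holds as a weak stated method together with an internal mismatch. Symptomatic harms rest on unsolicited reports filtered by the woman's own view of cause; a study-level rule depends on those reports; and the listed report contents carry neither adverse events nor the triggering count. Under-counting is the likely direction, so the rule is not assured to act when severe diarrhea has reached the level it is meant to catch. Differential reporting by arm is a plausible bias for symptoms and injuries.

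The mismatch and the trigger of 32 in 160 rest on the article, the latter with all randomized women as denominator. The size of under-counting is unknown: the 20% / r figures and the probabilities illustrate sensitivity to assumed inputs and do not predict what this trial would see. This is a worthwhile, inexpensive improvement, not a defect that invalidates the design.

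**What to change.** 1. **Collection (Safety and Data Monitoring, and Table 1).** Ask all four arms the same short set of questions, whether or not the woman links the event to the intervention: gastrointestinal symptoms including diarrhea severity, falls, and musculoskeletal injury. Ask at baseline and week 12, and preferably at one brief remote contact in between. Spontaneous reports continue alongside.

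2. **Monitoring report.** Add cumulative adverse-event counts by arm, and the running number of women with severe diarrhea beside the number randomized so far.

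3. **Reconciliation.** Make the trigger, the way reports are collected and the report contents consistent with one another, including which count and denominator the rule is read on and when it is looked at. The trigger itself is for the trial team; no change to it is proposed here.

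Possible wording: *All participants in the four groups will be asked the same questions about gastrointestinal symptoms, falls and injuries at baseline, at one remote contact and at week 12, irrespective of perceived cause. Monitoring reports will give cumulative adverse events by group and the running count of participants with severe diarrhea.*

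**Cost.** A short form and, with one remote contact per woman, about 160 brief calls or messages by the existing team. No extra visit or sample is needed. Prompted questions will record more minor symptoms, which need a little more handling and should be reported as solicited.

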#### Dissemination

A lay summary of the report will be communicated to all study participants. The results of the study will also be disseminated at various seminar presentations and feedback sessions at the College of Health, School of Health Sciences, Massey University, Palmerston North, New Zealand, and in manuscripts that will be submitted to a peer-reviewed journal.

### Strengths and Limitations of This Study

This study was designed as an RCT to account for exercise history, and the sample size and duration have been selected to ensure an adequately powered sample needed to detect clinically and statistically significant results. In this study, investigating the effects of both prebiotics and probiotics with and without weight-bearing exercise provides strong evidence for an RCT. The limitation of the study lies in the inability to extend the duration in terms of further follow-up.

### Conclusions

Our research study aims to decrease the possibility of osteoporotic fractures resulting because of the incidence of inflammation and loss of bone mass by improving body composition (lean and fat mass) among postmenopausal women after ≥5 years. This study compares the effectiveness of synbiotic supplementation and weight-bearing exercise intervention, both of which may be used as a therapy for bone health maintenance in postmenopausal women. To the best of our knowledge, this will be the first RCT to analyze the effects of both a synbiotic supplement and an exercise intervention in postmenopausal women. On the basis of the results obtained, a combination of synbiotic supplementation and exercise might serve as a noninvasive approach to manage and/or improve body composition and bone health in postmenopausal women.

## Abbreviations

ANOVA: analysis of variance
BMD: bone mineral density
COMP: cartilage oligomeric matrix protein
CTx-I: cross-linked C-telopeptide of type 1 collagen
DXA: dual-energy x-ray absorptiometry
ELISA: enzyme-linked immunosorbent assay
HRT: hormone replacement therapy
hs-CRP: high-sensitivity C-reactive protein
IL: interleukin
P1NP: procollagen type 1 N-terminal propeptide
QALY: quality-adjusted life-year
RCT: randomized controlled trial
SCFA: short-chain fatty acid
TNF: tumor necrosis factor
